### 2.9. Data Management and Monitoring

Data will be collected electronically via an encrypted online database tailored to each study procedure, including eligibility, and baseline and post-intervention assessments. No identifying information will be stored in this database. Instead, a unique identification code generated by a random number sequence, will be assigned to each participant in an independent table, ensuring a pseudonymized process. Access to all information will be restricted to a corporate computer and only principal investigators will be authorized to access the data. This process is in place to ensure fidelity of therapy and to ensure that any confidential content is managed in accordance with the protocol. After data entry, a thorough assessment of data consistency will be performed, and any omissions or inconsistencies will be addressed as necessary. Study updates and general results will be communicated to participants via a newsletter.

### 2.10. Statistical Methods

The comparability of the study groups will be assessed by the similarity of the distribution of the variables of interest at baseline. The analysis will follow standard methods for randomized controlled trials, using two-group comparisons for all participants on an intention-to-treat basis. The chi-squared test or Fisher´s exact test will be used to compare proportions. Student´s *t*-test will be used to compare means between groups with normally distributed data. The Mann–Whitney test will be used to compare quantitative variables between groups in the case of a non-normal distribution, as determined by the Kolmogorov–Smirnov test. Correlations between quantitative measures will be determined by Spearman’s rho correlation coefficient. Matched pair data analysis is also calculated. In addition, multivariate analysis will be performed using multiple linear regression and logistic regression, depending on the response under consideration. This will allow for adjustment of the effectiveness of the intervention for potential confounders and the identification of other variables associated with each of the outcomes. Statistical significance will be set at ≤0.05. Data will be analyzed using the Statistical Package for the Social Science (SPSS) software, version 27.0 (IBM Corp, Armonk, New York, NY, USA).

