### 2.7. Study Timeline

All participants will attend baseline assessments (post-allocation, T1) prior to randomization into the groups and will be re-assessed at the end of the study period after 8 weeks (close-out, T2). The study schedule is shown in Table 3.

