### 2.8. Sample Size

Based on a review of the literature [35,36], people who undergo an exercise therapy program show improvements such as improved quality of life and functionality. Therefore, the sample size was calculated based on the primary outcomes: SF-36 and FM-UE.

Previous studies have shown that a difference of 12.4 points with an SD of 5 points in the FM-UE score is required to detect the minimum clinically important difference between the two study groups [37,38].

Furthermore, Norman et al. conclude that the threshold for detecting changes in health-related quality of life is approximately 5 points [39]. Taking into account the possible number of subjects we could recruit, the sample size is calculated to detect an improvement of 5 points in the summary components of the SF-36 questionnaire with a standard deviation (SD) of 5 points. The SD value was taken as half that of the general population (SD = 10) because we considered our sample to be more homogeneous. To detect this difference between the groups with a 95% confidence interval and 80% power for a bilateral approach, we would need 16 subjects. If we estimated a 15% attrition rate, the final sample size would be 18 subjects in each group.

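### The two-group tests promised for all participants by intention to treat use only those with a T2 score, and without baseline adjustment they are open to bias if dropout depends on baseline differently by arm

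*Protocol article*

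**What the plan says.** Section 2.10 sets the population as two-group comparisons "using two-group comparisons for all participants on an intention-to-treat basis". For quantitative outcomes, Student's t-test "will be used to compare means between groups with normally distributed data", and the Mann–Whitney test "will be used to compare quantitative variables between groups in the case of a non-normal distribution". The section does not say whether T2 scores or changes from T1 are compared. It then adds that "multivariate analysis will be performed using multiple linear regression and logistic regression, depending on the response under consideration", to adjust for potential confounders. Those confounders are not named, and the T1 score of the outcome is not fixed as a covariate.

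Section 2.7 gives one follow-up: participants "will be re-assessed at the end of the study period after 8 weeks (close-out, T2"). Table 3 confirms that SF-36 and FM-UE are measured at T1 and T2 only.

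Section 2.8 plans for losses: "If we estimated a 15% attrition rate, the final sample size would be 18 subjects in each group".

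The article has no rule for a participant without a T2 score. The sentence in section 2.9 about dealing with omissions concerns consistency checks after data entry.

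**The concern.** The stated population and the stated tests do not match. A t-test or Mann–Whitney test, on T2 or on change, needs an observed T2 value. So does a matched-pair analysis. Run as named, with nothing added, these tests leave out the participants whom section 2.8 expects to lose, while the result would be reported as intention to treat for everyone.

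The arms give different reasons to leave. Participants know their allocation (section 2.3), and sET adds sixteen 60-minute group sessions that UC does not have (section 2.4). If the kind of participant who leaves differs by arm, the remaining groups are no longer balanced at baseline, and an unadjusted test carries that imbalance into the estimated effect. The T1 score that could correct for it is already collected, but the main comparison is not required to use it.

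**Working it through.** **The plan's own figures**

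Section 2.8 aims to "detect an improvement of 5 points in the summary components of the SF-36 questionnaire with a standard deviation (SD) of 5 points", two-sided 5%, 80% power.

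- n per group = 2 × (1.96 + 0.84)² × (5/5)² = 15.7, so 16. The stated 16 is reproduced.
- 16 / 0.85 = 18.8, so 19. The stated 18 is one lower, which is immaterial here.
- Expected without T2: 0.15 × 36 = 5.4 participants, or 0.15 × 18 = 2.7 per arm. I use 3 per arm.
- SE of an unadjusted difference with 15 per arm: 5 × √(2/15) = 1.83 points.

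**Assumptions not in the documents**

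Losses are split evenly, the correlation ρ between T1 and T2 is 0.5 or 0.7, scores are normal, there is no true effect, and leaving depends on the T1 score in the patterns below. The article gives only the 15% total. SD 5 is the planning value in section 2.8 for both primary outcomes.

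**Size of the bias by formula**

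In a sample of 18 from a normal distribution, the three lowest values average 1.41 SD below the mean. The other 15 therefore average 3 × 1.41 / 15 = 0.28 SD above it, which is 0.28 × 5 = 1.41 points at baseline (0.282 before rounding).

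- T2 t-test, lowest three leave sET and UC losses are random: bias = ρ × 1.41 = +0.70 (ρ = 0.5) or +0.99 (ρ = 0.7).
- Change-score t-test, same pattern: bias = (ρ − 1) × 1.41 = −0.70 or −0.42.
- Opposite losses (lowest three leave sET, highest three leave UC): both double, to +1.41 or +1.97 for T2 and −1.41 or −0.85 for change.
- Lowest three leave both arms, or losses are random: bias = 0.

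**Check by simulation** (8,000 replicates per case; bias in points, then rejection rate at 5%; each pair is ρ = 0.5 / 0.7)

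| Loss pattern | T2 t-test | Change t-test | ANCOVA on T1, those with T2 |
|---|---|---|---|
| Random | 0.00 / 0.00; 5% / 5% | 0.02 / −0.01; 5% / 5% | 0.01 / −0.01; 5% / 5% |
| Low baseline, sET only | +0.70 / +0.98; 7% / 9% | −0.68 / −0.42; 7% / 6% | 0.01 / −0.01; 5% / 5% |
| Opposite by arm | +1.43 / +1.97; 14% / 22% | −1.40 / −0.88; 13% / 10% | 0.02 / −0.04; 5% / 5% |

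**What removes the bias**

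The unbiased column also uses only participants with T2, so baseline adjustment does the work. A T1–T2 mixed model with a common baseline mean gives the same treatment estimate. Its likelihood splits into a part for T1 and a part for T2 given T1 and arm, and participants with T1 only inform the first part alone.

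**Precision**

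With random loss, the simulated SE falls from 1.82 to 1.60 (about 12%) at ρ = 0.5 and from 1.84 to 1.33 (about 27%) at ρ = 0.7. The theoretical ratio √(1 − ρ²) gives 13% and 29% before the small cost of estimating the slope. The gain is smaller when losses unbalance the arms at baseline.

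**The case against.** The strongest objection is that much of this is silence. The article nowhere restricts the analysis to completers, imputation before a t-test would fit its wording, and missing-data rules are commonly left to an analysis plan, which is not shown here. That stands. A reader might infer that the plan prescribes a completers-only analysis, or that intention to treat is contradicted outright. The documents do not support either. What remains is narrower: the named tests do not by themselves deliver the stated property, and the main comparison does not have to use the baseline score.

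A reader might also infer that the bias would favour sET. The sign depends on whether T2 or change is tested, which section 2.10 does not say, and on dropout patterns for which the article has no figure.

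Nor is it shown that losing the participants with T1 only causes the bias. ANCOVA on those with T2 is unbiased in every pattern tried, so a model that nominally keeps all 36 has no advantage over it for the treatment estimate.

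Two further points are fair. Planned regression could give the protection if it included T1, but this is not fixed and it is listed as an addition. Retention is also partly addressed already: T2 reassessment is planned for all, calls are made every two weeks in both arms (Table 2), and UC participants may join the program after T2.

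The 70% attendance criterion in Table 1 also sits badly with intention to treat. It is a separate matter, and this point would remain without it.

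**Conclusion.** The point holds in a limited, conditional form. Unless values are imputed, the named two-group comparisons cover those with T2, about 31 of 36 at the planned attrition, and should not be described as covering all participants. They are biased only if leaving depends on the baseline score differently by arm. Under the assumed patterns, one-arm loss shifts a T2 t-test by about 0.7 to 1.0 points, which is 14% to 20% of the 5-point target, and raises the error rate to 7% to 9%. The extreme opposite-loss case reaches about 2.0 points and 22%. The direction in practice is not known, and the bias is zero if losses are random or alike in both arms.

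The case for change does not rest on these scenarios alone. Baseline adjustment also improves precision when losses are random. It does not protect against dropout that depends on the unseen T2 score.

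**What to change.** In section 2.10:

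1. Make the main analysis of SF-36 and FM-UE a comparison of T2 scores by randomized arm adjusted for the T1 score. ANCOVA is enough; a T1–T2 mixed model with a common baseline mean gives the same treatment estimate.
2. State that missing T2 values are assumed missing at random given baseline and arm.
3. Add one sensitivity analysis that shifts the T2 values filled in for sET leavers until the conclusion changes. With 3 of 18 missing, a shift of 5 points moves the estimate by 5 × 3/18 = 0.83 points.
4. If an unadjusted test is kept, describe it as a comparison of participants with a T2 score, not as intention to treat for all participants.

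The cost is a few rewritten sentences and one more model in the SPSS software already named. No visits, staff or participants are added. The downside is slightly more analysis work and a conclusion that rests openly on a missing-data assumption.

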### 2.3. Allocation and Blinding

After completion of the baseline assessment, independent, centralized, stratified block randomization will be used to allocate participants to either the intervention or the control group. Randomization will be performed using a computer-generated random number sequence, with a 1:1 allocation ratio. The assessors involved in eligibility, pre- and post-intervention assessments, and statistical analysis will be blinded to group allocation throughout the entire study period. Due to the nature of the trial, it is not possible to blind intervention parties, including both participant and program staff, to their group assignments.

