Health-related quality of life (SF36)		X	X
Upper extremity motor function (FM-UE)		X	X
Functional capacity: gait endurance (6MWT)		X	X
Functional capacity: gait velocity (10MWT))		X	X
Mobility (TUG)		X	X
Balance (BBS)		X	X
Physical Activity (GPAQ)		X	X

SF36: Short-Form 36 Questionnaire; FM-UE: Fugl-Meyer Upper Extremity Assessment Scale; 6MWT: Six-Minute Walk Test; 10MWT: Ten-Meter Walk Test; TUG: Timed Up and Go Test; BBS: Balance Berg Scale; GPAQ: Global Physical Activity Questionnaire.

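### The planned between-group test is valid but inefficient: a t-test or Mann–Whitney test chosen by a normality pre-test, where one baseline- and strata-adjusted ANCOVA would gain precision and fix what is estimated

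*Protocol article*

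**What the plan says.** Section 2.10 plans two-group comparisons by intention to treat. Means are compared by Student's t-test when the data are normal. The Mann–Whitney test "will be used to compare quantitative variables between groups in the case of a non-normal distribution", and a Kolmogorov–Smirnov test on the trial data decides which case applies. The section then adds "Matched pair data analysis is also calculated" and, as a further step, multiple linear or logistic regression. Of the regression it says: "This will allow for adjustment of the effectiveness of the intervention for potential confounders". No confounder is named, and the same models are also meant to identify other variables associated with the outcomes. "Statistical significance will be set at ≤0.05".

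Section 2.3 states that "independent, centralized, stratified block randomization will be used to allocate participants". Section 2.7 and Table 3 show that both primary outcomes, SF-36 and FM-UE, are measured at baseline (T1) and after 8 weeks (T2).

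Section 2.8 sizes the trial to "detect an improvement of 5 points in the summary components of the SF-36 questionnaire with a standard deviation (SD) of 5 points", and concludes that "with a 95% confidence interval and 80% power for a bilateral approach, we would need 16 subjects". Allowing for 15% attrition, it arrives at 18 per group.

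**The concern.** The trial will hold a baseline value of each primary outcome and at least one stratification factor for every participant. The between-group tests described cannot take a covariate, so they make no use of the strata, and they use baseline only if they are run on change scores, which section 2.10 does not say. The regression could use both, but it comes second and its covariates are left open.

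The normality switch raises a separate matter. The t-test addresses a difference in means and the Mann–Whitney test a shift in ranks. When a pre-test on about 16 observations per arm decides between them, the data settle what the trial estimates.

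Precision and a clearly defined estimate are at stake. Both matter here because section 2.8 says the sample size took account of how many subjects could be recruited, so lost power is hard to win back with more participants.

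**Working it through.** **Inputs.** From section 2.8: difference 5, SD 5 (d = 1), two-sided, 80% power, 16 per group before attrition, and the general-population SD of 10 that the plan halves. From section 2.10: significance level 0.05. The correlation r between baseline and T2 is not in the documents. It is assumed, over 0.3 to 0.8.

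**1. The plan's own figure.** n = 2 × (1.960 + 0.842)² × (5/5)² = 15.7, so 16 per group, as stated. For attrition, 16 × 1.15 = 18.4 and 16/0.85 = 18.8, against the stated 18. The sample size therefore rests on an unadjusted comparison of two means.

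**2. Power at 16 analysed per arm, SD 5 at T2.** Noncentral t, noncentrality = (5/s) × √(16/2), with:

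- T2 t-test: s = 5, 30 df
- change-score t-test: s = 5√(2(1 − r)), 30 df
- ANCOVA on baseline: s = 5√(1 − r²), 29 df

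| r | T2 t-test | Change-score t-test | ANCOVA | Residual variance, ANCOVA |
|---|---|---|---|---|
| 0.3 | 78.1% | 63.8% | 81.7% | 91% |
| 0.5 | 78.1% | 78.1% | 88.4% | 75% |
| 0.6 | 78.1% | 86.4% | 92.7% | 64% |
| 0.7 | 78.1% | 94.2% | 96.9% | 51% |
| 0.8 | 78.1% | 99.1% | 99.5% | 36% |

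**3. If the SD of 5 is already a change-score SD.** Then 5 = SD(T2) × √(2(1 − r)), and the ANCOVA residual SD is 5√((1 + r)/2): 4.03 at r = 0.3 and 4.74 at r = 0.8. The change-score t-test has 78.1% power throughout. ANCOVA gives 92%, 88%, 86%, 84% and 82% for r = 0.3, 0.5, 0.6, 0.7 and 0.8.

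**4. If the T2 SD is 10 (d = 0.5).** Unadjusted power is 27.8%. ANCOVA gives 30.0%, 35.2%, 40.1%, 48.2% and 62.5% over the same values of r.

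**5. The pre-test.** Simulation of 20,000 trials per shape, 16 per arm, switching to Mann–Whitney if normality is rejected in either arm. The article does not say whether the Lilliefors correction applies, so both versions are shown.

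| Data shape | Switches, Lilliefors | Switches, uncorrected | Two-stage type I error (Lilliefors) | t-test and Mann–Whitney disagree on significance at d = 1 |
|---|---|---|---|---|
| Normal | about 10% | under 0.1% | 5.1% | 6% |
| Chi-square, 4 df | 45% | 1% | 5.3% | 10% |
| Lognormal, sigma 0.5 | 48% | 1.6% | 5.4% | 11% |
| Exponential | 73% | 4.3% | 5.5% | 13% |

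For clearly skewed data of the two middle kinds, the corrected pre-test is close to a coin toss. The uncorrected version hardly ever switches, so it does not do the job it was given. Either way, type I error stays close to 5%.

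**The case against.** The strongest reply is that nothing here makes the result wrong. An unadjusted comparison in a randomized trial is unbiased, and its standard error already allows for chance baseline imbalance. Leaving out the strata tends to make the standard error too large, which is conservative. The two-stage rule barely inflates type I error. All of that stands.

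A reader might infer that the plan ignores baseline scores. The text does not support that: section 2.10 is silent on T2 versus change scores, and section 2.8 speaks of an improvement of 5 points, so a change-score analysis is a plausible reading. Under it the gain from ANCOVA is smaller at high correlations: 2.7 points at r = 0.7 (94.2% to 96.9%) and 0.4 points at r = 0.8.

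A reader might also infer several rival answers with no order among them. That goes too far. The choice between t-test and Mann–Whitney follows a stated rule, paired tests do not estimate the between-group effect and are nowhere offered as efficacy evidence, and the regression is placed after the two-group comparison. The real discretion lies in the regression covariates.

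Finally, a journal article may leave covariate lists and the names of strata to a fuller document, so their absence is not held against the plan. What remains is what the article does fix: a data-chosen test as the main comparison, with adjustment as an add-on. The article never labels that comparison primary; its status is read from the wording and order of section 2.10.

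**Conclusion.** The point holds as one of efficiency and of a clearly defined estimate, not of validity. At the plan's effect and 16 per arm, ANCOVA raises power from 78.1% to between 81.7% and 99.5% if the test would have been on T2 scores with SD 5, and from 78.1% to between 82% and 92% if the SD of 5 describes change scores. With a T2 SD of 10, power rises from 27.8% to between 30.0% and 62.5%, so adjustment helps but does not rescue the trial. ANCOVA exceeds both t-tests at every correlation checked.

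The size of the gain depends on a correlation that the documents do not give; at r = 0.3 it is only 3.6 points over a T2 t-test. The gain from adjusting for strata is not quantified, because the factors are not named. The Kolmogorov–Smirnov switch does little harm to type I error. Its fault is that it selects between two different quantities, and does so unreliably at this sample size.

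**What to change.** In section 2.10, name one primary analysis for each primary outcome: an ANCOVA of the T2 score on arm, the baseline value of that outcome and the randomization stratification factor(s), in all randomized participants, reporting the adjusted mean difference with a 95% CI. Keep the covariates to these, given about 32 people analysed.

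Drop the Kolmogorov–Smirnov switch, and name a bootstrap or permutation version of the same model as the sensitivity analysis for non-normal data. Label regressions with selected confounders and within-group paired tests as exploratory.

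The change should be made before outcome data by arm are seen. It costs a few degrees of freedom and a rewording. No new data are needed, and section 2.10 already plans multiple linear regression, of which ANCOVA is a case.

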## Abstract

Introduction: Acquired brain injury (ABI) constitutes a significant and growing global public health concern. People with ABI often face a range of physical and psychosocial challenges that span the domains of “body structure and function”, “activity”, and “participation”, as defined by the International Classification of Functioning, Disability, and Health. Multidisciplinary approaches based on exercise therapy with social leisure activities are essential to improve physical recovery and health-related quality of life after injury. Methods: Adults with ABI, aged > 18 years, in the subacute or chronic stage (within more than one month after the injury) will be recruited through a rehabilitation center. Adults will be randomized to receive either a racket sports-based exercise therapy program combined with usual care (sET) or usual care alone (UC) using a random number sequence with a 1:1 allocation ratio. sET intervention consists of an 8-week exercise therapy program focusing on different racket sports skills, 1 h in duration, 2 days/week. It will be delivered by a physiotherapist in tailored, face-to-face, group-based sessions. Primary outcomes will be the health-related quality of life (SF-36) and upper extremity motor function (Fugl-Meyer Assessment-Upper Extremity Scale). Discussion: The study proposes an intervention that combines sports-based exercise therapy with usual care. It aims to determine whether this intervention improves the health-related quality of life and upper limb motor function in adults with ABI compared with usual care alone. The results of this study may have clinical implications for the rehabilitation of this population.

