### 2.6. Outcome Measures

#### 2.6.1. Primary Outcome Measures

36-item Short Form Health Survey (SF-36) version 2

This instrument assesses general health in eight domains: physical function, role physical, bodily pain, general health, vitality, social function, role emotional and mental health. Scores above or below 50 (the normative score from the general population) are interpreted as better or worse than the reference population, respectively. This questionnaire has a high validity and test–retest reliability [28].

Fugl-Meyer Upper Extremity Assessment Scale (FM-UE)

The FM-UE is a performance-based index used to assess motor impairment in the upper extremities. It assesses movement of the biceps, triceps, shoulder, elbow, forearm, hand, wrist and finger by performing of 33 tasks. Clinicians rate the patient’s performance on each task for quality of movement on a scale from 0 (no active movement) to 2 (movement appears normal). The maximum score is 66 points, and a high score indicates less impairment. The FM-UE has excellent psychometric properties, including high inter-rater reliability and excellent test–retest reliability and responsiveness [29].

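### SF-36 and FM-UE are both primary at an undivided 0.05, with no success rule and no single primary SF-36 score

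*Protocol article*

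**What the plan says.** - **Two primary outcomes.** The Abstract states: "Primary outcomes will be the health-related quality of life (SF-36) and upper extremity motor function". Section 2.6.1 lists both instruments as primary, and section 2.8 says that "the sample size was calculated based on the primary outcomes: SF-36 and FM-UE". Neither is ranked above the other.
- **One threshold.** Section 2.10: "Statistical significance will be set at" 0.05 or below. The level is not split or ordered, and no rule says what counts as a positive trial.
- **SF-36 in the outcome section.** Section 2.6.1: "This instrument assesses general health in eight domains". It lists the domains and does not mention a summary score.
- **SF-36 in the sample size.** Section 2.8 aims to "detect an improvement of 5 points in the summary components of the SF-36 questionnaire with a standard deviation (SD) of 5 points", and does so "with a 95% confidence interval and 80% power for a bilateral approach". The plural is left open, and no one component is named. Table 3 lists only the questionnaire.

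**The concern.** A two-sided 5% level protects the primary conclusion only if that conclusion rests on one pre-named test, or on several tests combined by a stated rule. Here at least two primary tests each use the full 0.05. The SF-36 part could mean one summary score or two, because section 2.8 uses the plural and section 2.6.1 does not settle it.

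Without a rule, a positive trial could be reported on whichever primary score crosses 0.05, and the choice of SF-36 score could be made after the results are seen. The nominal 5% would then not describe the risk of a false primary claim. It would also be unclear which score the stated 80% power refers to.

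**Working it through.** **Step 1. Reproduce the plan's sample size, to see which alpha was used.** Inputs from section 2.8: difference 5, SD 5, two-sided, 80% power.

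n per group = 2 × (SD/difference)² × (z for 1 − alpha/2 + z for power)²

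- alpha 0.05: 2 × 1² × (1.960 + 0.842)² = 15.7, so 16. This is the stated figure.
- alpha 0.025: 2 × 1² × (2.241 + 0.842)² = 19.01, so 20.

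The stated 16 therefore comes from the full 0.05, with no allowance for a second primary outcome.

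**Step 2. Count the primary tests.** The count is derived, because the article does not state it.

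- One SF-36 score plus FM-UE: 2 tests.
- Two summary components plus FM-UE: 3 tests. This assumes that the plural in section 2.8 means two.

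**Step 3. Chance of at least one false primary result**, each test at 0.05, no true effect on any score, and any one success counting. For k independent tests this is 1 − 0.95^k. For correlated tests it was simulated with equally correlated normal test statistics. The documents give no correlation, so a range is assumed.

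| Assumed correlation | 2 tests | 3 tests |
|---|---|---|
| 0 | 9.75% | 14.3% |
| 0.3 | 9.5% | 13.6% |
| 0.5 | 9.1% | 12.5% |
| 0.7 | 8.3% | 10.9% |

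**Step 4. What Holm would cost.** Inputs: 16 per arm; SF-36 standardised difference 5/5 = 1; FM-UE standardised difference 12.4/5 = 2.48 (both from section 2.8); two-sample t-test.

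| Quantity | Power |
|---|---|
| SF-36 at 0.05, unadjusted | 78% |
| SF-36 at 0.025 | 68% |
| FM-UE at 0.025 | above 99.9% |
| SF-36 under Holm, FM-UE effect as planned (simulated) | about 78% |
| SF-36 under Holm, FM-UE with no effect (simulated) | about 68% |

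Under Holm, once FM-UE passes at 0.025, SF-36 is tested at 0.05. With the planned FM-UE effect this almost always happens, so the adjustment takes essentially nothing from SF-36. The unadjusted 78% is a t-test figure. The normal approximation behind the plan's 16 gives 81% at 0.05 and 72% at 0.025, so the two methods should not be mixed when the loss is stated.

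**The case against.** **The success rule is not in the text.** The article nowhere says that either outcome is enough. Its Abstract and Introduction join quality of life and upper-limb function with an "and", which could mean that both are required. If both were required, each on one fixed score, the error would be at most 5%. This stands, and it makes every rate above conditional. It does not remove the point, because the article does not state that rule either, and the SF-36 score is not fixed. If either of two summaries could satisfy the SF-36 half, that half alone would carry up to 1 − 0.95² = 9.75%.

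**A multiplicity rule is often left to an analysis plan.** That is true, and its absence alone would not be a finding. But this article fixes an undivided 0.05, sizes the trial with it, and leaves the primary SF-36 score open between sections 2.6.1 and 2.8.

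**A reader might infer nine primary tests**, eight domains plus FM-UE, and an error rate of up to 1 − 0.95^9 = 37%. The documents do not support this as the main reading. Section 2.6.1 describes what the questionnaire covers, just as it describes FM-UE by its 33 tasks, which nobody would take as 33 endpoints. The only place that ties SF-36 to a score for inference is section 2.8, and it refers to summary components. The 37% also needs eight domains of one questionnaire to be independent. At assumed correlations of 0.3 to 0.7 the nine-test rate is about 33% to 20%. These figures apply only if all eight domains were treated as primary.

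**A reader might also infer that correcting the error rate cuts power to 68%.** That holds for a fixed split at 0.025. Under Holm with the plan's own FM-UE assumption it does not hold.

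**Conclusion.** The point holds in a limited form. Two outcomes are primary at an undivided 0.05, no rule says whether one or both must succeed, and no single SF-36 score is named as primary. If any one primary success may be claimed, the chance of a false primary result is about 8% to 10% (two tests) or 11% to 14% (three tests), against the nominal 5%.

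These rates rest on three assumptions: the either-outcome rule, which the documents do not state; no true effect on any primary score; and equal correlations of 0.7 down to 0, which are not taken from the documents. The missing SF-36 score and the undivided alpha can be read from the text and do not depend on these assumptions.

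**What to change.** Before unblinding:

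1. Name one SF-36 summary component as the primary SF-36 score. Which one is the investigators' choice.
2. Make the other summary component and the eight domains secondary.
3. Test the named score and FM-UE with Holm at an overall two-sided 5%: the smaller p-value against 0.025 and, if it passes, the other against 0.05. This also settles the success rule, because either outcome can then be claimed with the error held at 5%.
4. Make sections 2.6.1, 2.8 and 2.10 agree, and state in 2.8 which score the power refers to.

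The cost is wording. Under the plan's assumptions SF-36 power stays at about 78% and no extra patients are needed. The downside is that if FM-UE has no effect, SF-36 power falls to about 68%, and section 2.8 should say so.
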